### Data Analysis

Baseline characteristics will be presented as counts and percentages for categorical measures. Continuous measures will be reported as means and SDs or medians and IQRs, as appropriate. Summary statistics by group will be provided for the primary and secondary outcomes and will be compared using 2-sample *t* tests, Wilcoxon rank-sum tests, or Fisher exact tests, as appropriate. Our intention-to-treat analysis will use linear mixed-effects models to assess the noninferiority of the single-visit intervention compared to the multivisit intervention, adjusting for baseline values of the primary outcomes. Additional intention-to-treat analyses will include any covariates that differed between groups at baseline. Primary outcomes will be the 4-week changes in measures of pain and function, and models will account for site using a random effect. Point estimates, CIs, and *P* values will be obtained for between-group differences in 4-week mean change compared to the margin of noninferiority. Significance for testing pain and function will be assessed at an *α* level of .025. We plan to report all data disaggregated by sex, AT type, and AT duration.

Secondary analyses will use linear mixed-effects models to examine predictors of improvement in pain and disability separately at 4 weeks. The same analysis will be performed at 12, 26, and 52 weeks as secondary end points. Outcomes will be the changes measured at each follow-up time point, and the models will be controlled for the corresponding baseline values. Model selection will be conducted to identify the optimal predictor set for each change outcome over time. The pool of candidate predictors includes baseline demographic and ultrasound imaging variables, as well as immediate improvement (within 2 weeks) of pain-related psychological factors, knowledge on self-management, pain, and disability. Models for all additional predictor combinations up to order 3 will be fit, and the Akaike information criterion will be calculated to compare model fits with the same outcome. Point estimates, CIs, and *P* values will be reported for predictors in models selected by the Akaike information criterion for each outcome. Significance for model predictors will be assessed at an *α* level of .05. Categorization of continuous variables using clinically meaningful cut points, such as obesity categories for the continuous BMI variable, will also be explored.

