### Outcome Measures

To maintain blinding of outcome assessment, baseline measures will be gathered in person prior to randomization. A research assistant blinded to the treatment groups will capture outcomes after randomization. Participants will complete 3 survey-only evaluation sessions at 2, 12, and 26 weeks. Participants will complete 3 video evaluation sessions, including surveys, at 4 weeks (primary end point), 8 weeks, and 52 weeks. The video evaluation sessions will be used to capture pain with tendon-loading activities (heel raises and hops) in real time, assess heel raise performance (number of heel raises), and screen for adverse events. A visualization of measure administration can be seen in Table 2.

**Table 2. T2:** Data collection schedule and format for both the self-guided and clinician-guided intervention groups over the duration of study participation.

Format of data collection	In person	Remote					
	Before the intervention	During the intervention			After the intervention		
	Week 0	Week 2	Week 4^a^	Week 8	Week 12	Week 26	Week 52
Randomization	✓						
Tendon Health Domains (Performance-based)	✓		✓	✓			✓
Tendon Health Domains (Survey-based)	✓	✓	✓	✓	✓	✓	✓
Ultrasound imaging	✓						
Clinical variables	✓		✓	✓	✓	✓	✓

a Week 4 indicates primary end point.

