### Power Calculation

The trial is powered to evaluate noninferiority between the two treatment groups at 4 weeks for 2 coprimary outcomes: (1) movement pain on a 0‐10 NRS, using a 1.1-point noninferiority margin, and (2) disability using the VISA-A, with an 8.2-point noninferiority margin. Both margins are consistent with previously published clinically meaningful thresholds [40]. Because the primary analysis will evaluate both outcomes using separate noninferiority tests, we applied a Bonferroni-adjusted, 2-sided *α*=.025 for each outcome. Power calculations assume comparison of mean group differences at 4 weeks using the same linear mixed-effects models planned for the primary analysis with adjustment for baseline values. A sample of 64 participants per group provides ≥80% power to conclude noninferiority for each outcome at *α*=.025. To account for an anticipated 20% dropout, we inflated the sample size to 80 participants per group.

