### Missing Data

Reasons for missing data will be recorded and compared qualitatively between participants who drop out and participants who complete the study. Participant characteristics collected prior to dropout will be compared to those of participants who complete the study. For the primary imputation strategy, if comparisons show that participant characteristics do not differ meaningfully between those with and without missing data, we will assume the data are missing at random and proceed accordingly. Under this assumption, we will use multiple imputation of the missing values for variables included in the linear mixed-effects models. Multiple imputation will be performed using SAS PROC MI and PROC MIANALYZE procedures in SAS software (version 9.4; SAS Institute Inc).

All variables in the primary analyses and, if feasible, other variables in the study database predictive of the missing values or influencing the cause of missing data will be included. For the sensitivity analyses addressing missing not at random, if assessment of reasons for missing data suggests that data may be systematically related to unobserved values (eg, inability to attend the next day assessment due to severe AT pain), sensitivity analysis will also be performed to assess the potential impact of including missing not at random data in the analysis. Methods for sensitivity analysis such as marginal delta adjustment, conditional delta adjustment, reference-based controlled imputation, and other pattern-mixture models will be considered. If needed, variables will be transformed to satisfy approximate normality before imputation and then retransformed to the original scale.

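### Unadjusted two-sample tests on the outcomes add a zero-difference P value to the noninferiority endpoints and are the only arm comparison stated for most secondary outcomes

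*Protocol article*

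**What the plan says.** The Data Analysis section describes three things that bear on arm comparisons or could be taken to.

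- **Two-sample tests.** "Summary statistics by group will be provided for the primary and secondary outcomes and will be compared using 2-sample". The procedures named there are the t, the Wilcoxon rank-sum and the Fisher exact test. No covariate is named, no visit is given, and the tests are not labelled descriptive.
- **The deciding analysis of the two primary outcomes.** "Our intention-to-treat analysis will use linear mixed-effects models to assess the noninferiority of the single-visit intervention compared to the multivisit intervention". The section describes this model as "adjusting for baseline values of the primary outcomes". Its P values concern "between-group differences in 4-week mean change compared to the margin of noninferiority". Testing of pain and function is set at an alpha of .025.
- **The other mixed models.** "Secondary analyses will use linear mixed-effects models to examine predictors of improvement in pain and disability separately at 4 weeks", and again at later visits. These look for predictors. They are not described as arm comparisons on the remaining secondary outcomes.

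Under Outcome Measures, "baseline measures will be gathered in person prior to randomization", and Table 2 ticks both the performance-based and the survey-based tendon health measures at week 0. The Power Calculation section sets the margins: for movement pain, "using a 1.1-point noninferiority margin", and for VISA-A, 8.2 points.

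**The concern.** There are two separate issues.

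**Primary outcomes.** A noninferiority trial asks whether the single-visit arm is worse by less than a margin. A two-sample test asks whether the difference is zero. A nonsignificant result from the second question says nothing about the first, yet the Introduction hypothesises that the single visit will be as effective as the multivisit programme. A P value that finds no difference could be read as support for that hypothesis in a trial where noninferiority was not shown.

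**Secondary outcomes.** For PROMIS scores, kinesiophobia, heel raises, quality of life and the like, the two-sample test is the only arm comparison the article gives. It is valid under randomisation, but less precise than a model that uses the baseline value already collected.

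**Working it through.** **Inputs.** Margins of 1.1 (NRS) and 8.2 (VISA-A), two-sided alpha of .025 per outcome, and 64 evaluable and 80 randomised per arm come from the Power Calculation section. The VISA-A SD of 16.3 is an assumption: it is printed beside the minimal important difference in Table 3, and the power section gives no SD. The baseline to follow-up correlation r is not in the document, so 0.3, 0.5 and 0.7 are used.

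**The plan's own figure.** n per arm = 2 × [SD × (z_alpha + z_power) / margin]².

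- One-sided 0.025: 2 × [16.3 × (1.960 + 0.842) / 8.2]² = 62.0, so 63 (64 with the t distribution). This reproduces 64.
- One-sided 0.0125 (the relevant tail of two-sided .025), unadjusted: 2 × [16.3 × (2.241 + 0.842) / 8.2]² = 75.1, so 76. With baseline adjustment, 64 suffices if 1 − r² is at most 64 / 75.1 = 0.852, that is, r of at least 0.385.
- Dropout: 64 / 0.8 = 80.

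An SD of 16.3 is therefore compatible with the stated size. The NRS figure cannot be checked, because no NRS SD is given.

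**Precision for secondary outcomes.** With equal variances at both visits, the variance of the baseline-adjusted estimate is 1 − r² relative to a test on follow-up scores. Relative to a test on change scores it is (1 − r²) / [2(1 − r)] = (1 + r) / 2.

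| r | against follow-up test | against change test |
|---|---|---|
| 0.3 | 0.91 | 0.65 |
| 0.5 | 0.75 | 0.75 |
| 0.7 | 0.51 | 0.85 |

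At r = 0.5, 128 evaluable participants act like 128 / 0.75 = 171. For an assumed difference of 0.4 SD with 64 per arm and two-sided 0.05, the unadjusted test has expected z = 0.4 × √32 = 2.263 and power Φ(2.263 − 1.960) = 62%. With adjustment, z = 2.263 / √0.75 = 2.613 and power is Φ(0.653) = 74%.

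**The zero-difference test on VISA-A.** SE = 16.3 × √(2/64) = 2.88. This is for follow-up scores; at r = 0.5 it is the same for change scores.

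- Single-visit arm truly worse by 8.2: z = 2.846. The test is nonsignificant in 1 − Φ(2.846 − 1.960) = 19% of trials at two-sided 0.05, and in 1 − Φ(2.846 − 2.241) = 27% at .025.
- Truly worse by 4.1: z = 1.423. It is nonsignificant in 70% at 0.05 and 79% at .025.

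**How often the two analyses would be read differently.** The adjusted noninferiority test is taken at one-sided 0.0125 and the follow-up-score difference test at two-sided 0.05. The correlation between the two estimates is √(1 − r²). The table gives the share of trials in which noninferiority is not shown and the difference test is nonsignificant.

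| True deficit | r = 0.3 | r = 0.5 | r = 0.7 |
|---|---|---|---|
| 0 | 20% | 12% | 3% |
| 4.1 | 48% | 43% | 33% |

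The opposite pattern, noninferiority shown with a significantly worse two-sample test, occurs in about 0.1% of trials at r = 0.5 for deficits of 0 to 4.1.

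**The case against.** The strongest case against runs as follows.

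- **The primary analysis is sound.** The mixed model adjusts for baseline and tests against the margin, and the trial is powered on that model. This stands. A reader might infer that the plan throws away baseline for the primary outcomes, or tests in the wrong direction. Neither is supported: the two-sample test has a different null, not a reversed direction, and no stated conclusion rests on it.
- **Baseline may enter through change scores.** The primary outcomes are defined as 4-week changes, and the sentence does not say which score is tested. This stands. It is why both columns of ratios are shown; a change-score test uses baseline, but less efficiently than adjustment for r below 1.
- **The alpha may be stated.** The .025 sentence on testing pain and function could cover these tests, so it would be wrong to say that none is given. Results at both levels are shown above.
- **The tests might concern baseline values only.** The sentence follows the baseline summaries, and a later sentence refers to covariates that differ at baseline. But it names the primary and secondary outcomes and is not limited to week 0, so this reading does not remove the problem.
- **Completers only?** The Missing Data section says "we will use multiple imputation of the missing values for variables included in the linear mixed-effects models". A reader might infer that the two-sample tests use completers only. The section does not say so, and it allows other variables into the imputation, so the point is left open.
- **The analysis plan may hold fuller secondary models.** It may. The point is therefore about the method this sentence states, not about models that are absent.

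**Conclusion.** The point holds at a modest level. On the primary outcomes the two-sample tests are a redundant P value against zero difference. It cannot inform the noninferiority question and could be misquoted, but the formal conclusion and the sample size are unchanged. On secondary outcomes other than pain and disability, the only comparison the article states is valid but inefficient, giving up 9% to 49% of the variance if follow-up scores are tested and 35% to 15% if change scores are tested, for r from 0.3 to 0.7.

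The ratios rest on the assumed r and on equal variances at both visits. The VISA-A figures also rest on SD 16.3 being the relevant SD and on 64 evaluable participants per arm. The percentages in the last table describe how often a misreading would be possible, not an error the plan commits.

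**What to change.** Change the sentence in Data Analysis in two ways.

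1. Present the primary outcomes by group descriptively, with no two-sample test, so that the noninferiority model is their only between-arm inference.
2. For each secondary outcome with a week-0 value, estimate the arm difference and its CI from the same baseline-adjusted model, with a suitable generalised model for categorical measures. Items with no natural baseline, such as the treatment credibility ratings, can keep a simple comparison.

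If the two-sample tests were meant only for week-0 values, the sentence should say so. The cost is a short text change and a little programming. No new data are needed and no power is lost.

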### Multivisit Group

Participants in the multivisit, PT-guided rehabilitation program will have 7 one-on-one telehealth visits over 8 weeks with a PT. These 30-minute visits will include exercise participation and education. Participants will be expected to complete 1 educational unit per week and will be given an exercise log to track exercises completed at home between treatment sessions. Instruction on exercise performance and progression will be provided by a PT throughout the plan of care. The PT will review the weekly educational content with the participant at each visit.

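### Ongoing physical therapist (PT) care exists only in the multivisit arm, but the noninferiority model and its power allow for site alone; if outcomes differ between PTs, the interval is too narrow for a conclusion beyond the participating PTs

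*Protocol article*

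**What the plan says.** Participants are randomised individually, 1:1, at two sites. Everyone first has an in-person visit with a PT, and allocation is revealed only after that visit (Overview; Randomization and Concealed Allocation). From then on the arms differ in structure. The single-visit arm works through the online units at its own pace (Single-Visit Group). Multivisit participants "will have 7 one-on-one telehealth visits over 8 weeks with a PT", and "Instruction on exercise performance and progression will be provided by a PT throughout the plan of care" (Multivisit Group).

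The primary analysis is a linear mixed model adjusted for baseline, and site is the only random effect named: "models will account for site using a random effect" (Data Analysis). Power is computed "using the same linear mixed-effects models planned for the primary analysis with adjustment for baseline values" (Power Calculation). The margins are stated as "using a 1.1-point noninferiority margin" for movement pain and "with an 8.2-point noninferiority margin" for VISA-A, with a "Bonferroni-adjusted, 2-sided *α*=.025 for each outcome". The sample size claim is that "A sample of 64 participants per group provides ≥80% power to conclude noninferiority for each outcome".

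The article does not give the number of PTs, an ICC or design effect, or whether one PT follows a participant throughout.

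**The concern.** This is a partially nested design. After allocation, multivisit participants who share a PT may share that PT's effect on outcome, while single-visit participants have no corresponding grouping. The site term shifts both arms equally, so it cancels from the arm difference and leaves any between-PT variance in the multivisit arm unaccounted for.

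In a noninferiority trial an understated standard error works against caution, because the interval clears the margin more often than it should. PT contact is also the component that the trial varies. The stated objective, a programme that widens access to care, suggests a conclusion meant to apply to PTs other than those who happen to take part.

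**Working it through.** **The plan's own figures.** The dropout step reproduces: 64 / (1 − 0.20) = 80 per group. The 64 can only be solved backwards, because the power section states no SD. With a true difference of 0, a two-sided α of 0.025 (z = 2.241 for the tail of 0.0125) and 80% power (z = 0.842), the largest residual SD that 64 per group supports is margin × √(64/2) / (2.241 + 0.842):

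- VISA-A: 8.2 × 5.657 / 3.083 = 15.05
- NRS: 1.1 × 5.657 / 3.083 = 2.02

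The only SD printed nearby is 16.3, beside the VISA-A minimal important difference in Table 3, and it is not declared as a power input. Taken unadjusted it gives 72.7% power at 64 per group. With an assumed baseline correlation of 0.4 it gives 80.6%. Because the plan adjusts for baseline and claims at least 80%, the working starts from 80%. All these figures assume independent participants.

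**Adding PT clustering in one arm.** Let k be the number of PTs, m = 64/k the participants per PT, and ICC the share of outcome variance between PTs. Both k and ICC are assumptions.

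- Design effect in the multivisit arm: DE = 1 + (m − 1) × ICC
- Factor on the standard error of the arm difference: f = √((1 + DE)/2)
- False noninferiority at the margin if PT is ignored: 1 − Φ(2.241/f)
- Power with the correct standard error: Φ(3.083/f − 2.241)

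Worked case, 4 PTs and ICC 0.05: m = 16; DE = 1 + 15 × 0.05 = 1.75; f = √(2.75/2) = 1.173. False noninferiority = 1 − Φ(1.911) = 2.8%. Power = Φ(0.387) = 65.1%.

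| ICC | PTs | DE | f | False noninferiority (nominal 1.25%) | Power (80% if independent) |
|---|---|---|---|---|---|
| 0.01 | 8 | 1.07 | 1.017 | 1.4% | 78.5% |
| 0.01 | 4 | 1.15 | 1.037 | 1.5% | 76.8% |
| 0.01 | 2 | 1.31 | 1.075 | 1.9% | 73.5% |
| 0.02 | 8 | 1.14 | 1.034 | 1.5% | 77.0% |
| 0.02 | 4 | 1.30 | 1.072 | 1.8% | 73.7% |
| 0.02 | 2 | 1.62 | 1.145 | 2.5% | 67.4% |
| 0.05 | 8 | 1.35 | 1.084 | 1.9% | 72.7% |
| 0.05 | 4 | 1.75 | 1.173 | 2.8% | 65.1% |
| 0.05 | 2 | 2.55 | 1.332 | 4.6% | 52.9% |

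**Does the site term help?** A simulation of 20,000 trials per setting used two sites, PTs nested in site, and a model with arm and site (site entered as a fixed effect). False noninferiority at ICC 0.05 was 4.7%, 2.8%, 2.1% and 2.0% for 2, 4, 6 and 8 PTs. At ICC 0.02 it was 2.4%, 1.8%, 1.6% and 1.5%. With no PT effect it was 1.0% to 1.3%. The site term does not remove the inflation.

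**Does the shared first visit matter?** When the simulated PT effect was shared equally by both arms, as from a common visit before allocation, the rate at ICC 0.05 was 1.1% to 1.2%. Only PT care after allocation, in one arm, causes the problem.

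**The case against.** The strongest reply is that this is detail a journal article leaves to the statistical analysis plan. That carries some weight: degrees of freedom, supportive models and provider terms often sit there, and the unseen plan may cover them. But the article does more than stay silent. It states the clustering level of the primary model and ties the power claim to that model.

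A reader might infer that the interval is too narrow as a matter of fact. The documents do not support that. They give no ICC, no number of PTs and no statement that each participant keeps one PT; if PTs rotate across visits, the nesting weakens. Several features point to a low ICC. Both arms share the same learning units and exercise progression. The primary end point is week 4 of an 8-week course, so only part of the telehealth visits has taken place. At ICC 0.01 with 4 to 8 PTs the effect is small.

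A reader might also infer that PT contact is confined to one arm. It is not. Everyone has the first visit, and Safety Monitoring and Reporting has clinicians and assessors in touch with both groups. The first visit precedes allocation, and the later contact common to both groups is for monitoring. The coached progression is what differs.

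Finally, if the conclusion is limited to the participating PTs, the inflation largely disappears. That is a legitimate choice of scope, but the article does not make it.

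**Conclusion.** The point holds conditionally. For any positive between-PT variance in the multivisit arm, the stated model understates the standard error for a conclusion reaching beyond the participating PTs, and the error favours noninferiority.

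Over the assumed range the consequence runs from slight (1.4% false noninferiority and 78.5% power with 8 PTs at ICC 0.01) to serious (4.6% and 52.9% with 2 PTs at ICC 0.05). These figures assume 64 analysed per arm, equal PT caseloads, one PT per multivisit participant, a true difference of 0 for power, and a normal approximation starting from 80%. The direction is firm; the size cannot be fixed from the document. The point merits a change to the plan but does not invalidate the design.

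**What to change.** 1. Record the treating PT or PTs for each multivisit participant. This is best done now: the Results section reports 15 enrolled as of January 2026, with enrolment running to 2028.
2. Keep the stated model as primary. For both coprimary outcomes, prespecify a supportive partially nested model with a PT random effect in the multivisit arm only, arm-specific residual variances, and Kenward-Roger or Satterthwaite degrees of freedom. Report its interval beside the primary one.
3. State in the power section that the quoted power assumes no PT clustering.
4. If there are too few PTs to estimate the variance, show the interval over a range of assumed ICCs and limit the conclusion to the participating PTs.

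The cost is one database field, a few sentences of analysis and power wording, and one extra model per outcome, with no added participants. The downside is a wider supportive interval and an imprecise PT variance when PTs are few. As an illustration, take VISA-A with SD 16.3, no baseline adjustment and ICC 0.05. A cluster-mean test with small-sample degrees of freedom had 58% power with 8 PTs and 44% with 4, against 65% and 57% by the normal approximation. This is one reason to keep the nested model supportive.

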**Conclusions:**

The PACE (Progressive Achilles Loading via Clinician e-Support) trial will identify a rehabilitation program focused on education and exercise for AT that expands access to care and will identify factors that predict responses to exercise and education.

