Recent evidence has shown that overtreatment of musculoskeletal disorders does not lead to improved outcomes. Hopewell et al [17] found that a single session of education and self-management advice with a PT was noninferior to 6 sessions of in-person progressive exercise in improving pain and function among individuals with subacromial shoulder pain. Similarly, Katz et al [18] found that a self-directed home exercise plan alone was noninferior to 14 sessions of PT-guided exercise and manual therapy for pain reduction in individuals with meniscal tear–related knee pain. AT is lacking in trials to gauge the minimal effective dosage of exercise interventions. Pivoting to expand access through novel care delivery pathways is now more feasible, given the evidence that pain and function can improve with focused minimal care [19].

Clinicians currently lack evidence-based prognostic factors to differentiate patients who will benefit from rehabilitation from those who are less likely to respond [20,21]. Given that 26% to 47% of individuals with AT proceed to injections or surgery [22-24], the identification of prognostic factors could inform more efficient and personalized care. For nonresponders to rehabilitation, delays in progressing to invasive treatments prolong Achilles tendon pain, waste patient time and health care resources, and increase the total number of limited duty days as multiple treatments are tried. There is a critical need for a large, prospective study to identify factors that predict which patients with AT are most likely to respond to rehabilitation.

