This trial’s objective is to identify a rehabilitation program focused on education and exercise for AT that expands access to care and to identify factors that predict responses to rehabilitation. Our aims are twofold: (1) to determine the efficacy of a single-visit, PT-initiated rehabilitation program compared to a multivisit, PT-guided telehealth rehabilitation program for AT and (2) to identify early prognostic factors for individuals who experience the greatest improvement in pain and disability by 4 weeks. We hypothesize that a single-visit, PT-initiated rehabilitation program with a self-guided intervention will be as effective in improving pain and disability as a multivisit, PT-guided telehealth intervention. We also hypothesize that individuals with greater immediate (within 2 weeks) improvements in self-efficacy, pain, and disability will obtain the greatest benefits from rehabilitation.

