## Methods

### Overview

Progressive Achilles Loading via Clinician e-Support (PACE) is a single-blind, noninferiority, 2-arm, parallel-group randomized controlled trial. Individuals with AT will be randomized to a single-visit, PT-initiated rehabilitation program or to a multivisit, PT-guided telehealth rehabilitation program. All participants will initiate care with a single synchronous in-person visit with a PT and have access to information on exercise and education materials via an online learning management system. Primary outcomes will be the numeric rating scale (NRS) for movement pain and the Victorian Institute of Sport Assessment–Achilles (VISA-A) score for disability.

We will enroll 160 individuals with AT across 2 sites: 1 military treatment facility and 1 civilian academic center. Outcomes will be assessed at 2, 4, 8, 12, 26, and 52 weeks, with the primary end point at week 4. Deviations to the protocol will be reported in real time on the Open Science Framework. This protocol is reported in accordance with the SPIRIT (Standard Protocol Items: Recommendations for Interventional Trials) guidelines [25].

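### Aim 2 can find prognostic factors for outcome during rehabilitation, not predictors of response to it, and its models as written do not name the randomised arm

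*Protocol article*

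**What the plan says.** The wording of the predictor work is mixed. In the Introduction the second aim is "to identify early prognostic factors for individuals who experience the greatest improvement in pain and disability by 4 weeks", and the Abstract's Objective also speaks of prognostic factors. In the same Introduction paragraph, however, the trial's objective is "to identify factors that predict responses to rehabilitation", and the hypothesis concerns which individuals "will obtain the greatest benefits from rehabilitation". The rationale is that clinicians lack factors "to differentiate patients who will benefit from rehabilitation from those who are less likely to respond", so that nonresponders can be spared delay before invasive treatment. The Abstract's Conclusions say the trial "will identify factors that predict responses to exercise and education", and the Discussion repeats the response wording.

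On design, the Overview states: "Individuals with AT will be randomized to a single-visit, PT-initiated rehabilitation program or to a multivisit, PT-guided telehealth rehabilitation program". Everyone starts with one in-person visit and has the same online exercise and education material. The arms differ in therapist contact: self-paced in one, weekly telehealth review of the units in the other.

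On analysis, the second paragraph of Data Analysis models change at each follow-up in linear mixed-effects models controlled for the baseline value. It says "The pool of candidate predictors includes baseline demographic and ultrasound imaging variables", together with two-week changes in psychological factors, self-management knowledge, pain and disability. Combinations of up to three predictors are compared by AIC. Neither the randomised arm nor any factor-by-arm term is mentioned in that paragraph.

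**The concern.** Whether someone responded to rehabilitation is a comparison with how they would have fared without it. This trial has no such comparison, because every participant is rehabilitated. Textbox 1 requires current pain of at least 3 out of 10, and the stratification allows symptoms of under 3 months, so some improvement is to be expected whatever is done. A factor associated with greater change may simply mark people who were going to recover faster.

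The intended use makes this matter. If a marker of slow natural recovery is reported as a marker of nonresponse, it could be used to move patients towards injection or surgery on the ground that rehabilitation does not work for them. These data cannot show that.

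The second, smaller issue is the randomised arm. Two-week changes are post-randomisation variables, and the therapist in the multivisit arm is already reviewing the content with participants by then. If arm affects both an early change and the later outcome, leaving it out adds an arm effect to the apparent predictive value of the early change. Self-management knowledge looks the most exposed.

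**Working it through.** **Inputs.** From the Power Calculation section: 64 completers per group, 80 per group after 20% dropout, VISA-A margin 8.2. From Randomization: 1:1 allocation. From Participant Selection: a female target of at least 33%, used here only as an example of an uneven factor. SD 16.3 is printed beside the VISA-A minimal important difference in Table 3. The power section gives no SD, so 16.3 is an assumption.

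**The plan's own figure.** 64 / 0.80 = 80 per group, 160 in total. With margin 8.2, SD 16.3, one-sided 0.025 and 80% power, n = 2 × (1.960 + 0.842)² × (16.3/8.2)² = 62.0, so 63 per group (64 using the t distribution). This agrees with 64, conditional on the SD and on that reading of alpha. No power figure is given for the predictor models; the calculations below use 128 completers.

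**1. Can the model tell natural recovery from response?** Take a 50/50 factor worth 8.2 points through natural recovery alone, equal in both arms and unrelated to treatment. The pooled coefficient has SE = 16.3 × √(1/64 + 1/64) = 2.88. Power = Φ(8.2/2.88 − 1.96) = Φ(0.89) = 0.81. A simulation of 4,000 trials gave the same: significant in 81% of runs. A purely prognostic factor is therefore readily selected, and nothing in the output distinguishes it from a predictor of response.

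**2. How much confounding does leaving out arm create?** Let arm shift both the two-week change and the outcome by d within-arm SDs, with no other link between them. With 1:1 allocation the variance of arm is 0.25, so

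correlation = 0.25d² / (1 + 0.25d²).

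- d = 0.5 (the margin, 8.2/16.3 = 0.50): 0.0625 / 1.0625 = 0.059, or 0.059² = 0.35% of variance.
- d = 0.25: 0.0156 / 1.0156 = 0.015.

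**3. What could factor-by-arm terms deliver?** For a binary factor with prevalence f, SE = SD × √(2/(64f) + 2/(64(1 − f))), and power at 8.2 points is Φ(8.2/SE − 1.96), two-sided 0.05.

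| Baseline correlation | f | SD | SE | Power |
|---|---|---|---|---|
| 0 | 0.50 | 16.3 | 5.76 | 30% |
| 0 | 0.33 | 16.3 | 6.13 | 27% |
| 0.5 | 0.50 | 16.3 × √0.75 = 14.1 | 4.99 | 38% |
| 0.5 | 0.33 | 14.1 | 5.31 | 34% |

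The interaction detectable with 80% power is 2.80 × SE, about 14 to 17 points.

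**4. Does the arm term undo dilution?** No. In the simulation, a factor worth 8.2 points in the multivisit arm only appeared in the pooled model as about 4.1 points and was significant in 28% of runs; the interaction test was significant in 29%. A main effect for arm leaves that averaged slope essentially unchanged, so dilution is not an argument for the arm term.

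**The case against.** The strongest reply has four parts.

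First, Aim 2 itself says prognostic, the Data Analysis section speaks of predictors of improvement, and the Discussion justifies the heterogeneous sample by reference to prognostic studies. The analysis fits that aim. This stands: the fault is in the wider claims, and the models of change are not the wrong tool for prognosis.

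Second, a reader might infer that the models definitely exclude the randomised arm. The article does not say so. The candidate list is introduced by a verb that need not be exhaustive, the same paragraph also does not repeat the site effect named for the primary analysis, and a condensed article may leave model terms to a fuller plan. The reliance on N=160 in the Discussion is compatible with an arm term. What remains is that the text states an adjustment and does not name arm in it; and if arm were merely a candidate, AIC selection could drop it.

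Third, baseline adjustment handles part of the regression to the mean, including the coupling of two-week and later change through a shared baseline. That is right. It does not remove natural recovery.

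Fourth, a reader might take the protocol to promise which patients need the extra visits, and fault it for lacking interaction tests. It makes no such promise, and it already plans to report data disaggregated by sex, tendinopathy type and duration. Nor would a factor-by-arm result be evidence of response to rehabilitation: both arms are rehabilitated, so it would show only whether added therapist guidance works differently in some patients.

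**Conclusion.** The claim to predict response to, or benefit from, rehabilitation goes beyond the design. That follows from two active arms sharing the same content with no untreated group; it rests on no assumed figure, and no unseen analysis plan can alter it. What the trial can deliver is what Aim 2's own sentence says: prognostic factors.

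The arm point is secondary. As written, the Aim 2 models adjust for baseline values and do not name arm, while some candidates are measured after randomisation. The likely distortion is small: a correlation of about 0.06 even if the arms already differ by 0.5 SD on both variables, a difference as large as the noninferiority margin and contrary to the trial's hypothesis. The documents do not support a reading in which the predictor results would be seriously biased by arm.

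The primary noninferiority comparison is unaffected. The interaction power figures depend on the assumed SD of 16.3 and on 64 completers per arm.

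**What to change.** 1. In the second paragraph of Data Analysis, state that the randomised arm is included in every Aim 2 model as a fixed term and is not subject to AIC selection.
2. In the Abstract's Conclusions, in the objective and hypothesis in the Introduction, and in the Discussion, replace the wording about predicting responses to, or benefits from, rehabilitation with *prognostic factors for outcome during rehabilitation*. The rationale may keep its description of the clinical need, but the trial should not claim to meet it.
3. Optionally, report a few prespecified factor-by-arm estimates with confidence intervals, labelled exploratory and described as a differential effect of added therapist guidance. Tendinopathy type and symptom duration are natural choices, since disaggregated reporting by both is already planned.

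The cost is one model term and a narrower claim, with no new data, visits or participants. With 15 participants enrolled as of January 2026 and enrolment expected to run to 2028, the change can be recorded well before analysis, for example on the Open Science Framework, where the protocol already commits to reporting deviations. If item 3 is taken up, its price is low precision, which should be stated with the results.
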